### Randomization and following procedures

The treatment assignment ratio is 1:1, fixed throughout the study. The allocation to heparin or placebo is defined by randomly permuted blocks of size 2, 4 and 6 generated by a random number generator (*ralloc *program, Stata co. 8.2, College Station, TX, USA). Complete treatments (four ampoules for each patient, marked with the same sequential number corresponding to the randomization scheme) are available in the emergency room's pharmacy center. The placebo is packed identically to the heparin sodium injection, and has the same color and volume as the heparin. Therefore, procedures for administration (i.e. loading dose and continuous infusion) are identical. Outcome measures are documented by medical research assistants masked to both the subject's intervention group assignment and the activated partial thromboplastin time (aPTT) values corresponding to specific days of the intervention period.

### Methods for dealing with potential adverse events

General treatment for patients is left up to the medical team in charge of each patient, according to clinical practice guidelines for infectious diseases and critical care available at the institution.

Basic considerations for dealing with potential adverse events are:

- Infusion should be suspended indefinitely if there are *new *signs or symptoms of hemorrhage such as bleeding from gums, nosebleeds, extensive bruising, evidence of purplish skin areas or gastrointestinal bleeding.

- Infusion should be suspended indefinitely if there is an otherwise unexplained drop of 50% or greater in platelet count, or an absolute platelet count below 30,000 cells per mm^3 ^any time during the study.

- Infusion should be interrupted 2 hours before any percutaneous procedure or major surgery, and should only be resumed 1 hour after a percutaneous procedure or 12 hours after major surgery. In presence of bleeding complications with any of these procedures, infusion can only be resumed after normal results in coagulation tests, and no less than 24 hours after the procedure

- Infusion should be interrupted indefinitely if aPTT test is prolonged more than 60 seconds at any time during the infusion period.

### Sample size

Length of stay may be considered a time to event end-point, with patient discharge alive as the outcome. Those who die during the hospital stay will be considered as competing risks for this analysis because they are not censored observations. With a median length of stay of 11 days, a type I error of 0.05 and a type II error of 0.2, the estimated number of patients required to detect a relative hazard of being discharged alive of 1.3 is 231 [32]. This number of events may be achieved with a total sample size of 310 patients, assuming an overall hospital mortality of 25%.

MOD score data correspond to the case of longitudinal data with correlated measurements, and as such require special considerations for calculation of power and sample size [33]. The table 3 shows different estimates of power under different assumptions of correlation among repeated observations (ρ) and differences in rate of change (Δ) with a fixed sample size of 310 participants. This sample size also will have an 80% power to detect a 50% relative reduction in the secondary outcome of overall 28-day mortality.

**Table 3 T3:** Power estimates for differences (Δ) in MOD score with a fixed sample size of 155 patients per group and selected values of correlation (ρ)

ρ Δ	3 points	2 points	1 point
0.8	100%	99%	98%
0.5	100%	98%	97%

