## Conclusion

The available literature in animal and human research, and the understanding of the molecular biology regarding inflammation and coagulation, supports a randomized clinical trial for the use of heparin in sepsis. Our study will provide appropriate power to detect differences in valid surrogate outcomes, and it will explore important preliminary data for efficacy regarding the clinical end-point of mortality.

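### The 231 live discharges behind the length-of-stay sample size are about half the total needed: 310 patients give about 51% power for a relative hazard of 1.3, not 80%

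*Protocol article*

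**What the plan says.** Hospital length of stay is one of two primary aims; the other is change in MOD score. The Sample size section of the protocol article treats length of stay as time to discharge alive, with in-hospital death as a competing risk. The inputs are "a type I error of 0.05 and a type II error of 0.2", a relative hazard of 1.3 and a median stay of 11 days, and the result is that "the estimated number of patients required to detect a relative hazard of being discharged alive of 1.3 is 231".

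The result is introduced as a number of patients, but the next sentence treats it as events: "This number of events may be achieved with a total sample size of 310 patients", on the assumption that 25% of patients die in hospital. Table 3 gives 155 patients per group, so 310 is the two-arm total and 231 is used as the event total over both arms.

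The Conclusion, and the same sentence in the abstract, then says: "Our study will provide appropriate power to detect differences in valid surrogate outcomes".

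**The concern.** A hazard ratio as modest as 1.3 usually needs well over 400 events for 80% power, so 231 looks too small by a factor of about two. If so, the trial would miss a true relative hazard of 1.3 about half the time, not one time in five as planned. A non-significant result on this primary outcome could then be read as evidence against an effect of 1.3 that the trial had only an even chance of detecting. The sample size of 310 is derived from this calculation. The MOD score and mortality power statements then take that size as given.

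**Working it through.** **Inputs from the protocol article**
- Type I error 0.05, type II error 0.2, relative hazard 1.3, hospital mortality 25% (Sample size).
- Allocation 1:1 (Randomization and following procedures).
- Log-rank test (Analysis plan).
- Final significance level 0.0471 after two interim looks (Interim monitoring); used only as a sensitivity check.
- Sidedness is not stated. Two-sided is my base case; one-sided is shown alongside.
- The median stay of 11 days does not enter the number of events required.

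**1. The plan's own chain**
- 231 / 0.75 = 308, rounded to 310; and 310 × 0.75 = 232.5 live discharges.
- This step is consistent only if 231 is the total for both arms.

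**2. Events required in total (two-sided 0.05, 80% power)**
- (1.960 + 0.842)² = 7.849.
- Freedman: 7.849 × [(1.3 + 1)/(1.3 − 1)]² = 7.849 × 58.78 = 461.3. Half is 230.7, which rounds to 231.
- Schoenfeld: 4 × 7.849 / (ln 1.3)² = 456.1. Half is 228.0.
- An exponential two-sample formula without censoring gives 231.8 per arm.
- One-sided 0.05: 364 (Freedman) or 360 (Schoenfeld) in total, rounded up.

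None of these gives 231 as a total. The printed figure is reproduced only as a per-arm number.

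**3. Power for a relative hazard of 1.3 with the events the trial will have**
- Schoenfeld, 231 events: Φ(√231/2 × ln 1.3 − 1.960) = Φ(0.034) = 51.3%.
- Freedman, 231 events: Φ(√231 × 0.3/2.3 − 1.960) = 50.9%.

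| Events | Two-sided 0.05 | One-sided 0.05 | Two-sided 0.0471 (Schoenfeld) |
|---|---|---|---|
| 231 | 50.9–51.3% | 63.2–63.6% | 50.3% |
| 232.5 | 51.2–51.6% | 63.5–63.9% | 50.6% |
| 310 (every patient discharged alive) | 63.2–63.7% | 74.3–74.7% | 62.7% |

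Ranges run from Freedman to Schoenfeld.

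**4. Effect detectable with 80% power at 231 events**
- Two-sided: exp(2.802 × 2/√231) = 1.446, about 1.45.
- One-sided: about 1.39.

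**5. Size needed for 80% power at 1.3, two-sided**
- Freedman: 462 / 0.75 = 616 patients.
- Schoenfeld: 457 / 0.75 = 609.3, so 610 patients.

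**6. Simulation check**

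Exponential discharge times with a discharge hazard of ln 2/11 per day in controls, relative hazard 1.3, the same death hazard in both arms set to give about 25% deaths overall, deaths censored at death, two-sided log-rank test, 10,000 runs:
- 155 per arm: mean 231.6 events, power 50.9%.
- 308 per arm: mean 460.5 events, power 80.0%.

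**The case against.** **The per-arm origin is an inference.** The article never labels 231 as per arm, and the match depends on the formula: 230.7 by Freedman but 228.0 by Schoenfeld. This stands, and the origin should be described as probable. The shortfall does not depend on it, because 231 total events are too few however the number arose.

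**Sidedness is not stated.** One-sided 0.05 raises power to 63–64% and lowers the detectable hazard to about 1.39. The 51% is therefore conditional on a two-sided test, but neither reading reaches 80%.

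**The 80% is not stated literally for this outcome.** For length of stay the article gives a type II error of 0.2; its explicit 80% refers to 28-day mortality. The two statements mean the same thing.

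**Deaths are competing risks.** This does not halve the events required. The plan already allows for deaths through the factor 0.75, and even 310 live discharges would not reach 80%. The simulation censors deaths, so it supports the log-rank calculation and does not examine other treatments of competing risks.

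**The claim of adequate power covers more than length of stay.** Table 3 makes a separate claim of 97–100% for MOD score. That is fair: the correction here concerns length of stay only.

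**The error does not bias the estimate or inflate the type I error.** True, but the stated operating characteristic of a primary outcome is still wrong.

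**Conclusion.** The figure is wrong as written. For a relative hazard of 1.3 with 1:1 allocation and a log-rank test at two-sided 0.05, a type II error of 0.2 requires about 456 to 461 live discharges in total, twice the 231 used. With 310 patients and 25% mortality the type II error is close to 0.5. The trial has the planned power only for a relative hazard of about 1.45.

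This assumes a two-sided test and about 75% discharged alive. If the test is one-sided, the shortfall is smaller but remains. That 231 is a per-arm figure taken as a total is the likely explanation, not a documented fact.

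**What to change.** Keep 310 patients and correct the text:

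- In the Sample size section, replace the length-of-stay statement with wording such as: *about 232 live discharges give about 51% power for a relative hazard of 1.3 and 80% power for a relative hazard of about 1.45 (log-rank, two-sided 0.05)*. State the sidedness explicitly.
- In the abstract and the Conclusion, qualify the power claim so that it does not promise 80% for a relative hazard of 1.3 on length of stay.
- Commit to reporting length of stay with the relative hazard and its confidence interval, and to not reading a non-significant result as ruling out 1.3. This is good practice given the true power, not something the arithmetic alone forces.
- Give the DSMB the corrected figure before its next review.

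The cost is a text correction in the protocol and later reports, and a less favourable power statement. No extra patients are required. Restoring 80% power for 1.3 would take about 610 to 616 patients, roughly double the plan.

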**Conclusion:**

The available literature in animal and human research, and the understanding of the molecular biology regarding inflammation and coagulation, supports a randomized clinical trial for the use of heparin in sepsis. Our study will provide appropriate power to detect differences in valid surrogate outcomes, and it will explore important preliminary data for efficacy regarding the clinical end-point of mortality.

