### Interim monitoring

An independent Data and Safety Monitoring Board (DSMB) comprising three members with expertise in statistics, epidemiology and critical care practice are responsible for the interim monitoring process. The statistician in the data-coordinating center is the only person with access to the blind and the full data and he provides the required information, both overall for the interim quality assurance and specific by treatment group (efficacy and safety) exclusively for the DSMB.

The first interim was conducted when the first 103 study participants completed their 28-day vital status evaluation -approximately 9 months after study recruitment began. The second interim analysis will be conducted when 206 patients have been enrolled, approximately 16 months after the study initiation. Stopping guidelines for efficacy monitoring were determined according to the modified O'Brien-Fleming procedure [34,35]. With this procedure, the values for statistical significance will be 0.0006 and 0.0151 in the first (α_1_) and second (α_2_) interim analyses, respectively, for a final significance (α) of 0.0471.

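### Table 3's power figures for the MOD score contradict each other: the 1-point and 2-point columns cannot both be right

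*Protocol article*

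**What the plan says.** Change from baseline in MOD score is one of the two primary aims. The Sample size section derives 310 patients from the other one, length of stay, using "a type I error of 0.05 and a type II error of 0.2". For MOD it then reports power under varying correlation and "differences in rate of change (Δ) with a fixed sample size of 310 participants". The table caption is "Power estimates for differences (Δ) in MOD score with a fixed sample size of 155 patients per group", and the Randomization section confirms equal arms: "The treatment assignment ratio is 1:1, fixed throughout the study".

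The printed powers are:

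| ρ | 3 points | 2 points | 1 point |
|---|---|---|---|
| 0.8 | 100% | 99% | 98% |
| 0.5 | 100% | 98% | 97% |

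The Conclusion of the abstract, repeated in the Conclusion of the article, states: "Our study will provide appropriate power to detect differences in valid surrogate outcomes".

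**The concern.** Only ρ and Δ vary in the table, so along a row everything that determines the standard error is constant. The signal-to-noise ratio is then strictly proportional to Δ. Going from 2 points to 1 should cut it in half, yet the printed power barely moves. That happens only when power is so close to 100% at both differences that neither would print as 97% or 98%.

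What is at stake is how a null MOD result is read. If power at 1 point really is 97–98%, a null result is good evidence against a 1-point effect. If it is 50–60%, the same result is inconclusive at that size. As printed, the reader cannot tell which applies.

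**Working it through.** **Inputs.** From the article: 155 per arm, Δ of 1, 2 and 3 points, and the six powers above. Assumed: two-sided α = 0.05 (the 0.05 is stated only for length of stay, without sidedness) and the same variance for every Δ in a row. The SD and the MOD measurement schedule are not given, so no cell can be reproduced forwards. The consistency check does not need them, because they enter every cell of a row through the same standard error.

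**Formula.** Power = Φ(Δ/SE − 1.960), with SE = SD_eff × √(2/155). Here SD_eff absorbs residual SD, number of measurements and ρ. Inverting gives Δ/SE = 1.960 + z(power).

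**Step 1: what each printed power implies.**

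| ρ | Δ/SE at 1 point | Δ/SE at 2 points | Ratio | Required |
|---|---|---|---|---|
| 0.8 | 1.960 + 2.054 = 4.014 | 1.960 + 2.326 = 4.286 | 1.07 | 2 |
| 0.5 | 1.960 + 1.881 = 3.841 | 1.960 + 2.054 = 4.014 | 1.05 | 2 |

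**Step 2: take the 2-point cells as right.**
- ρ = 0.8: Δ/SE at 1 point = 4.286/2 = 2.143; power = Φ(0.183) = 57%. Letting 99% stand for 98.5–99.5% gives 54–62%. Implied SD_eff is 4.11.
- ρ = 0.5: Δ/SE at 1 point = 4.014/2 = 2.007; power = Φ(0.047) = 52%. Letting 98% stand for 97.5–98.5% gives 50–54%. Implied SD_eff is 4.39.
- At 3 points both rows give 100% after rounding, as printed.

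**Step 3: take the 1-point cells as right.**
- ρ = 0.8: Δ/SE at 2 points = 8.03; power = Φ(6.07), above 99.9999%. Implied SD_eff is 2.19.
- ρ = 0.5: Δ/SE at 2 points = 7.68; power = Φ(5.72), above 99.9999%. Implied SD_eff is 2.29.
- At 3 points both rows again give 100%. The 3-point column therefore fits either reading and cannot decide between them.

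**Step 4: can rounding or α rescue the table?** With the most favourable rounding the ratios are 4.535/3.920 = 1.16 (ρ = 0.8) and 4.130/3.772 = 1.09 (ρ = 0.5), still far from 2. A search over SD_eff found no value that fits either row within rounding at two-sided 0.05, two-sided 0.0471 or one-sided 0.05. The 0.0471 comes from the Interim monitoring section ("for a final significance (α) of 0.0471"). The 1-point power implied by the 2-point cells under other choices is:

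| Test | ρ = 0.8 | ρ = 0.5 |
|---|---|---|
| Two-sided 0.05, normal | 57% | 52% |
| Two-sided 0.05, noncentral t | 57% | 52% |
| Two-sided 0.0471 | 57% | 51% |
| One-sided 0.05 | 63% | 58% |
| Two-sided 0.025 | 52% | 46% |

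**Step 5: difference detectable with 80% power.** This needs Δ/SE = 1.960 + 0.842 = 2.802. Under Step 2 it is 2.802/2.143 = 1.31 points (ρ = 0.8) and 2.802/2.007 = 1.40 points (ρ = 0.5). Under Step 3 it is 2.802/4.014 = 0.70 and 2.802/3.841 = 0.73 points. The two readings differ by almost a factor of two.

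**Step 6: comparison between rows.** This step needs a further assumption: variance proportional to (1 − ρ), the standard form for a slope or change score. Δ/SE then differs between rows by √(0.5/0.2) = 1.581. A power of 98% at ρ = 0.8 would imply Φ(4.014/1.581 − 1.960) = Φ(0.579) = 72% at ρ = 0.5, not 97%. Conversely, 97% at ρ = 0.5 would imply above 99.9% at ρ = 0.8. The rows do not agree on this model either. This is supporting evidence only; the contradiction within rows does not depend on it.

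**The case against.** The strongest reply is that the error may be harmless. If the 1-point column is correct, the printed 97–98% stands and the only fault is that two cells are 1–2 percentage points too low. A single SD_eff of about 2.1–2.4 puts every cell within 2 points of its printed value, whereas the other repair moves two cells down by more than 40 points. Nothing in the article gives an SD that would favour the larger correction. This stands: the 50–60% figure is conditional. It does not reconcile the table, because such an SD_eff gives 100% where 99% and 98% are printed.

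Four further points deserve weight.
- The sample size does not rest on Table 3. The 310 patients come from length of stay, so a corrected table changes no design feature. This is true, but the table still supports the power claim for a primary outcome.
- The sentence on appropriate power covers both surrogate outcomes and names no 1-point target. On either reading, power at 2 points is at least the printed 98–99%. So the sentence is not refuted; it needs qualifying only if 1 point is meant to be covered and is not.
- Constant variance within a row is an inference, since the method is in a cited reference that is not at hand. It is the natural reading, because the text names only ρ and Δ as varying.
- A condensed article may leave the SD and visit schedule to the full protocol. Their absence is not the fault raised here; the conflict is between the printed numbers themselves.

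**Conclusion.** The concern holds. Given a common variance within each row, the 1-point and 2-point columns of Table 3 are incompatible, and no choice of α, sidedness, rounding or measurement schedule that was examined removes the conflict. At least one column is wrong.

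The size of the error depends on which. If the 2-point column is right, 1-point power is 57% and 52% at two-sided 0.05 (46–63% over the α choices examined), so the printed values are too high by 98 − 57 = 41 and 97 − 52 = 45 percentage points. If the 1-point column is right, the 2-point cells should read 100% and the table understates power by 1–2 points. The article cannot settle this, so the printed 97–98% at 1 point is unsupported rather than shown to be false. Because the table is the only power support shown for a primary outcome, it has to be corrected.

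**What to change.** Recompute all six cells of Table 3 from one formula and replace them. Give with the table the inputs that let a reader check it: residual SD, number and timing of MOD measurements, ρ, 155 per arm, and the α level and sidedness (0.05, or the final level after the interim looks). State also whether Δ is a difference in MOD score, as in the caption, or in its rate of change, as in the text, and over what time unit. Add the smallest difference detectable with 80% power. If 1 point is not covered, qualify the sentence on appropriate power in the abstract and in the article's Conclusion.

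The cost is one recalculation and a corrected table, with a possibly less favourable power figure. Sample size, analysis and conduct are unchanged.

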### Interim monitoring

An independent Data and Safety Monitoring Board (DSMB) comprising three members with expertise in statistics, epidemiology and critical care practice are responsible for the interim monitoring process. The statistician in the data-coordinating center is the only person with access to the blind and the full data and he provides the required information, both overall for the interim quality assurance and specific by treatment group (efficacy and safety) exclusively for the DSMB.

The first interim was conducted when the first 103 study participants completed their 28-day vital status evaluation -approximately 9 months after study recruitment began. The second interim analysis will be conducted when 206 patients have been enrolled, approximately 16 months after the study initiation. Stopping guidelines for efficacy monitoring were determined according to the modified O'Brien-Fleming procedure [34,35]. With this procedure, the values for statistical significance will be 0.0006 and 0.0151 in the first (α_1_) and second (α_2_) interim analyses, respectively, for a final significance (α) of 0.0471.

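### The three printed significance thresholds (0.0006, 0.0151, 0.0471) spend about 5.24% two-sided at the stated looks, not the planned 5%

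*Protocol article*

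**What the plan says.** In the protocol article, the Sample size section plans the length-of-stay comparison with "a type I error of 0.05 and a type II error of 0.2" and arrives at 310 patients in total. It does not say whether tests are one- or two-sided.

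The Interim monitoring section gives the stopping rule: "Stopping guidelines for efficacy monitoring were determined according to the modified O'Brien-Fleming procedure". It then gives the numbers: "the values for statistical significance will be 0.0006 and 0.0151 in the first" and second interim analyses respectively, "for a final significance (α) of 0.0471".

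The same section fixes the timing of the looks. For the first: "The first interim was conducted when the first 103 study participants completed their 28-day vital status evaluation", at about 9 months. For the second: "The second interim analysis will be conducted when 206 patients have been enrolled, approximately 16 months after the study initiation". The section does not name the endpoint to which the thresholds apply.

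**The concern.** A group-sequential boundary exists to keep the overall type I error at its planned level across all looks. When the numerical thresholds are printed, they can be checked against that level. These have the O'Brien-Fleming shape, but they sit slightly below the height that three equally spaced looks need at 5%. If so, the rule given to the monitoring board and used at the final analysis does not deliver the 0.05 on which the trial was sized, and a borderline final result could be called significant when it should not be.

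The two looks are also triggered differently, one by completed follow-up and the other by enrolment. If the second look carries less information than the boundary assumes, the error moves further in the same direction.

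**Working it through.** **Inputs.** Overall type I error 0.05 and total 310 patients (Sample size). Thresholds 0.0006, 0.0151 and 0.0471, with looks at 103 and 206 patients (Interim monitoring). Patient counts stand in for information, because no endpoint is named: 103/310 = 0.332 and 206/310 = 0.665, or about 1/3 and 2/3. Two-sided tests are assumed first.

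**Step 1: what the printed values are.** With z = Φ⁻¹(1 − p/2), the thresholds are z = 3.432, 2.430 and 1.985. An O'Brien-Fleming boundary has critical values C/√t. The implied constants are:
- look 1: 3.432 × √(1/3) = 1.981
- look 2: 2.430 × √(2/3) = 1.984
- final: 1.985 × 1 = 1.985

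Run forwards, C = 1.985 gives p = 0.0006, 0.0150 and 0.0471. This reproduces the plan's figures to within 0.0001, so the boundary family is clear.

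**Step 2: what they spend.** Under the null, the three z statistics are jointly normal with correlation √(tᵢ/tⱼ) for tᵢ < tⱼ. The overall error is the probability that at least one |Z| exceeds its critical value. Recursive numerical integration at t = 1/3, 2/3, 1 gives, for first crossing at each look:

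0.0006 + 0.0147 + 0.0370 = 0.0524 (the unrounded total is 0.05239).

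A multivariate normal calculation gives 0.0524, and a simulation of 20 million trials gives 0.0524. With t = 103/310, 206/310, 1 the total is again 0.0524.

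**Step 3: what 5% needs.** Solving for the constant at an overall 0.05 gives C = 2.004, so z = 3.471, 2.454, 2.004 and p = 0.0005, 0.0141, 0.0451. If looks 1 and 2 stay at 0.0006 and 0.0151, the final critical value that holds 0.05 is z = 2.009, or p = 0.0445.

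**Step 4: other readings.**

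| Reading | Result |
|---|---|
| Rounding of the printed values, lower and upper limits | total 0.0523 to 0.0525 |
| Printed values are one-sided p-values | total 0.0514 |
| Lan-DeMets O'Brien-Fleming-type spending, two-sided form | would print 0.0007, 0.0161, 0.0439 |
| Same, as twice a one-sided 0.025 | would print 0.0002, 0.0120, 0.0463 |
| Second look moved later, first look at 0.33 | total reaches 0.0500 only at about 0.80 of the information |

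Neither spending version matches the printed set. A second look at 0.80 does not fit 206 of 310.

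**Step 5: the trigger.** Taking a month as 30.4 days, 28 days is 0.92 months. Having 103 patients with completed status at 9 months implies 103/(9 − 0.92) = 12.7 enrolled per month. Then 206 are enrolled at about 16.2 months and have 28-day status at about 17.1 months. The stated 16 months therefore fits enrolment. At that moment about 12.7 × 0.92 = 12 patients lack 28-day status. If the boundary governs 28-day mortality, the second information fraction is (206 − 12)/310 = 0.63 and the total error is about 0.0531.

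**The case against.** The strongest reply is about size. The excess is 0.24 percentage points, or 0.14 on the one-sided reading. No sample size or endpoint changes, and the final decision differs only for p-values in a band 0.0471 − 0.0445 = 0.0026 wide. That is correct, and it makes this a small correction. It does not make the printed values right. The method is called modified and cites sources not available here, but no version tried at the stated schedule returns 5%.

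A second reply concerns the trigger, and most of it stands. A reader might infer that the newest patients at the second look have no outcome and that the true error is therefore 5.31%. The article does not support this as a general statement. It rests on applying the boundary to 28-day status, and 28-day mortality is a secondary outcome. For length of stay, with the stated median of 11 days and an assumed exponential stay, about 7 patients would still be in hospital (12.7/30.4 per day × 11/ln 2 days). Those patients still contribute censored time to a log-rank test. The article also fixes only when the second look takes place. It does not say which patients enter it or whether data mature first, and an article may leave that to the full protocol or board charter. Even on the 28-day reading, the trigger adds only about 0.07 points.

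A reader might also take the standard boundary's 0.0451 as the final limit under the present plan. That value goes with 0.0141 at the second look. With 0.0151 there, a final threshold of 0.0451 would spend 0.0506; the 5% limit is 0.0445.

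**Conclusion.** The concern holds for the threshold arithmetic. As printed, the three thresholds spend about 5.24% two-sided or 5.14% one-sided for a single endpoint, against a stated 5%. A final p between about 0.0445 and 0.0471 would be declared significant although the plan has no error left to support it.

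The direction holds on every reading tested that is consistent with looks at 103 and 206 of 310. The exact size rests on three assumptions: the tests are two-sided, patient counts represent information, and the 0.05 in the Sample size section is the overall level that the boundary is meant to hold.

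The difference in triggers is a secondary point that needs clarifying. The figure of about 5.3% applies only if the boundary is used for 28-day mortality. This is an inexpensive correction, and it does not suggest that the trial's conclusions would be unreliable.

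**What to change.** Keep 0.0006 for the look already held, and adopt one of the following before the second look:

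- 0.0141 at the second look and 0.0450 at the final analysis (overall 0.0500);
- 0.0151 at the second look and 0.0445 at the final analysis (overall 0.0500);
- an error-spending function evaluated at the information actually observed at each look.

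State whether the p-values are two-sided and which endpoint the boundary governs. Either trigger the second look when 206 patients have completed 28-day status, as was done for 103 at the first, or compute the boundary at the observed information.

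The cost is a change to the monitoring rule and a slightly stricter final threshold: 0.0450 or 0.0445 in place of 0.0471. Aligning the trigger would delay the second look by about one month; computing the boundary at the observed information avoids that delay.
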